### Randomization and Blinding

Participants will be randomly assigned to either the intervention or waitlist control group using a computer-generated randomization procedure. The Random Allocation Software developed by [name] [52] will be used to facilitate this process. Block randomization will be implemented to ensure balanced group sizes, with a maximum of 8 participants per group. Randomization will be carried out by an independent researcher who is not part of the current research team or is listed as an author. The principal investigator remains blinded to group assignments to maintain objectivity and reduce potential bias. Outcome measures are managed by a separate research assistant who is not involved in the delivery of the intervention, ensuring independence and reducing potential bias. Once a sufficient number of eligible participants have been recruited, randomization will be conducted, typically 2 weeks before the intervention start date. Participants will then be informed of their group allocation, along with the schedule of their assigned group sessions, by the designated research assistant. In alignment with the ongoing recruitment process and rolling admission, the intervention will be delivered to participants as they are randomized and assigned to groups.

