### Sample Size Calculation

Dingle and Fay [6] found a medium effect size (η^2^_p_=0.076) for improved emotion regulation after the music intervention with young adults, compared with the control group. Based on this medium effect size, at least 98 participants are needed to detect a significant group × time interaction effect (*P*<.05). However, based on previous trials, some dropout is expected after the intervention has commenced. The estimated attrition rate is 15%. Besides, considering that partnerships with middle schools have only recently begun to develop, while many university students have already expressed interest in committing to the project, we expect to recruit more university participants. Therefore, we aim to recruit over 100 participants for the randomization stage, including around 50 adolescents and 65 young adults, to account for possible dropouts before the intervention begins.

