### Description of the Intervention

The project consists of 5 weekly sessions: 1 introductory (preassessment) session followed by 4 psychoeducational sessions. Each session lasts approximately 60-90 minutes.

In the introduction session, participants sign the informed consent forms after being informed about the program’s content and expectations by the main group facilitator (ie, the research assistant). For participants under 18 years of age, parental consent will also be obtained during the session. Following the signing of consent, the baseline survey will be distributed and collected. Participants’ demographic information will be gathered through the survey. This includes, but is not limited to, age, gender, education level, household income, region of residence, living arrangement, and employment status.

Each week, participants will receive WhatsApp (Meta Platforms, Inc.) text message reminders about upcoming sessions and other important announcements.

The psychoeducational sessions differ in theme but follow a similar structure. Session 1 focuses on emotions located in various quadrants of the 2D model, such as high-arousal and negative-valence emotions. Session 2 explores happiness and loneliness, with the new component of loneliness added to this session. Sessions 3 and 4 address high-arousal emotions, such as stress and anxiety. An example session plan is provided in Multimedia Appendix 1 for reference (Table 1).

**Table 1 table1:** Summary of session content.

Session	Content
Session 1	Emotions located in various quadrants of the 2D model, such as high-arousal and negative-valence emotions
Session 2	Happiness and loneliness
Session 3	High-arousal and negative-valence emotions, such as stress and anxiety
Session 4	High-arousal emotions, such as perfectionism and anxiety (continue) and achievement

For the new loneliness component, in addition to discussing songs that evoke a sense of receiving empathy, psychoeducation will be provided on the positive effects of music sharing in building and strengthening emotional bonds in relationships [12]. The group sessions will offer a safe and pleasant environment where participants can talk about music, using this topic as a channel to foster new connections with fellow group members. In session 2, participants will be guided to discuss how they can apply this skill outside of the program to strengthen existing relationships and build new connections.

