### Data Analysis

For the main outcome evaluation measures, mixed measures ANOVAs will be performed. The between-participants factor is group (intervention vs control), and the within-participants factor is time (pre- vs postintervention). Before the main analyses, independent samples *t* tests (2-tailed, paired) will be conducted on the baseline demographic variables to identify any significant differences between the 2 groups. Any variables that show statistically significant differences will be included as covariates in the subsequent main analyses. It is expected that the treatment group will demonstrate improved emotion regulation and reduced mood symptoms and loneliness following the music intervention, compared with the control group. A medium effect size is anticipated for the significant group × time interaction effect.

All verbal and written feedback will be analyzed using thematic analysis [61]. The qualitative analysis software NVivo (QSR International) will be used to assist with the process. Content analysis will be conducted following the transcription and coding of the data.

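### Treatment is given in interacting groups of at most 8, but the planned ANOVA and the sample size of 98 assume independent participants; with any within-group correlation the error bars are too small and power is overstated

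*Protocol article*

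**What the plan says.** **Delivery.** Randomization and Blinding allocates individuals by computer, in batches as enough are recruited, and caps group size: "Block randomization will be implemented to ensure balanced group sizes, with a maximum of 8 participants per group". With a target above 100, the cap of 8 can only refer to therapy groups, not to trial arms. The section on music interventions and youth loneliness lists group work among the core components and calls each component essential. Description of the Intervention has participants talking about music, "using this topic as a channel to foster new connections with fellow group members".

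**Control arm.** Under Study Design, controls have only waited at their main second assessment; their sessions come later.

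**Analysis.** Data Analysis specifies mixed ANOVAs: "The between-participants factor is group (intervention vs control), and the within-participants factor is time (pre- vs postintervention". The only possible additions are demographic variables that differ significantly at baseline. There is no term for therapy group.

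**Sample size.** Sample Size Calculation says an earlier trial of the programme "found a medium effect size (η^2^_p_=0.076) for improved emotion regulation after the music intervention", and from this that "at least 98 participants are needed to detect a significant group × time interaction effect". It gives no ICC, design effect or group size. Attrition is put at 15%, and the target is around 50 adolescents plus 65 young adults.

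**The concern.** Members of one therapy group share sessions, discussion and each other, and the programme intends them to influence one another. Their changes in outcome may therefore be more alike than those of unrelated participants. Because only the intervention arm has been treated in groups at the main comparison, the design is partially nested: clusters in one arm, essentially single individuals in the other.

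An ANOVA that ignores this counts every intervention participant as a full independent observation. If the ICC is above zero, the standard error of the group × time term is too small, the nominal 5% test rejects a true null hypothesis too often, and 98 participants carry less information than the calculation supposes. This affects the primary outcome (DERS) and the secondary mood and loneliness outcomes, all analysed with this model. It also matters for the larger trial that this pilot is meant to inform, which would need an ICC for its own sample size.

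The protocol is not merely silent here. It names the model and its factors and it states a sample size, and both rest on independence.

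**Working it through.** **Inputs.** From Sample Size Calculation: partial eta squared 0.076, significance level 0.05, N = 98, attrition 15%, target 50 + 65. From Randomization and Blinding: at most 8 per group. Assumed: two-sided test, 1:1 allocation, groups of 7 or 8, equal total variance in both arms, and an ICC on the change score of 0.01, 0.05 or 0.10.

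**1. Reproduce 98.** In a 2 × 2 design the group × time interaction equals a two-arm comparison of change scores.
- f² = 0.076/(1 − 0.076) = 0.0823; f = 0.287; standardised difference d = 2f = 0.574.
- Noncentral F with 1 and N − 2 df and λ = N·f². Power is 0.798 at N = 97 and 0.803 at N = 98.

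So 98 is exactly the independent-participant answer at 80% power (85% would give 112 and 90% would give 130). The target leaves 115 × 0.85 = 97.75 completers. It covers attrition and nothing else.

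**2. Type I error of the planned ANOVA.** With clustering in one of two equal arms:
- DE = 1 + (m − 1)·ICC
- variance ratio VR = (DE + 1)/2
- type I error = 2·[1 − Φ(1.96/√VR)]

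Example, m = 8 and ICC 0.05: DE = 1 + 7 × 0.05 = 1.35; VR = 1.175; √VR = 1.084; 1.96/1.084 = 1.808; type I error 7.1%.

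**3. Power when the groups are respected.** With k groups:
- v = DE/nT + 1/nC
- Satterthwaite df = v² / [(DE/nT)²/(k − 1) + (1/nC)²/(nC − 1)]
- noncentrality = d/√v

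Example, 7 groups of 7 against 49 controls and ICC 0.05: DE = 1.30; v = 1.30/49 + 1/49 = 0.0469; √v = 0.217; df = 17.5; noncentrality = 0.574/0.217 = 2.65; critical t = 2.105; power about 70%. For 6 groups of 8 against 48 controls, df = 14.3 and power is about 68%.

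| Assumed ICC | Type I error, planned ANOVA | Power, small-sample df | Power, no df penalty | Interval width relative to planned |
|---|---|---|---|---|
| 0.01 | 5.4% | 74-76% | 78-79% | 1.07-1.09 |
| 0.05 | 6.8-7.1% | 68-70% | 73-75% | 1.14-1.18 |
| 0.10 | 8.6-9.2% | 60-64% | 67-69% | 1.22-1.29 |

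The type I column spans groups of 7 and 8 with 49 per arm. The other columns span 7 groups of 7 against 49 and 6 groups of 8 against 48. The last column is (critical t × √v) divided by 1.985 × √(2/49).

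**4. Simulation check** (20,000 runs). With 6 groups of 8 against 48 controls, the independent analysis rejected a true null in 7.0% of runs at ICC 0.05 and 9.5% at ICC 0.10. With 7 groups of 7 against 49 controls, it did so in 6.7-6.8% and 8.5-8.6%, while an analysis respecting the groups held 5.1-5.4%.

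**5. Rolling batches.** With a batch effect shared by both arms (variance 0.10) and ICC 0, the unadjusted test rejected in 4.1% of runs, which is conservative.

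**The case against.** **The size is conditional.** The protocol gives no ICC. At 0.01 the distortion is negligible, and at zero there is none. The protocol describes one music therapist and one research assistant; if that pair runs every group, facilitators add no between-group variance. A manual and session checklists also limit it. This stands. A reader might infer that the p-value is certainly too small, but the documents support only the conditional statement. They equally give no ground for taking the ICC as zero, and the stated mechanism points the other way.

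**It is a pilot on a seed grant.** True, and at low ICC the distortion is modest. A variance estimated from six or seven groups is also imprecise. But the protocol sets formal hypotheses and a powered test, so the test should have the error rate it claims.

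**Stronger readings that do not hold.**
- Recruiting and randomising in batches might seem to add to the inflation. It does not: when both arms come from each batch, ignoring batch is slightly conservative (step 5).
- Applying the design effect to both arms would overstate the problem, since controls have only waited. Whether they attend the introductory session in groups is not stated; if they do, a little clustering could arise there.
- The protocol does not say that the groups are closed, and the point does not need it.
- Quoting 73-75% power at ICC 0.05 would be too favourable for the recommended analysis, because it keeps about 96 degrees of freedom where 14-18 apply.

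**Conclusion.** The point holds in conditional form. The analysis and sample size as written assume independence, while the intervention is delivered in interacting groups. For ICCs of 0.01 to 0.10, the actual type I error of the planned test runs from about 5.4% to 9.2%, and power at about 98 completers runs from about 76% down to 60%, against the implied 80%. These figures rest on the assumed ICC range, groups of 7 or 8, about 49 completers per arm, clustering in the intervention arm only, and 80% as the intended power. The model should be corrected before the data are analysed.

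**What to change.** - **Model.** Replace the arm-by-time ANOVA with a partially nested linear mixed model: a random therapy-group effect in the intervention arm only, controls entered as singletons, and Satterthwaite or Kenward-Roger degrees of freedom.
- **Power.** Keep the enrolment target. State the power of 98 completers over an ICC range using those degrees of freedom, for example 74-76%, 68-70% and 60-64% at ICC 0.01, 0.05 and 0.10.
- **Reporting.** Report the observed ICC with its uncertainty, for planning the larger trial.
- **Batch.** Adjustment is an optional precision step. It should not be a mandatory fixed factor if each batch supplies only one intervention group. With seven groups that would leave about 6 degrees of freedom and power of about 60% at ICC 0.05.

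**Cost.** This changes analysis wording only; therapy-group membership is known from the session schedules. The price is wider intervals (about 1.07 to 1.29 times the planned width over this ICC range) and a less favourable stated power. Part of that price is the loss of degrees of freedom, which is paid even if the true ICC is small.

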### Participants

The target population for this study comprises post–high school students and adolescents aged 16-19 years. This age range aligns with international guidelines, such as those from the World Health Organization, which defines adolescence as ranging from 10 to 19 years, and the United Nations, which considers individuals aged 15-24 years as adolescents and young adults. Recruitment materials for the project will be disseminated to students in their final year of high school as well as recent graduates who maintain connections with their schools. Young adults, primarily those in their first year of undergraduate studies (typically aged 17-19 years in the Hong Kong context), will be recruited through posters displayed on university campuses and word-of-mouth referrals. A snowball sampling method will also be used to expand participant recruitment. Consistent with the approach used by Dingle and Fay [6], this study will include youth who self-report experiencing symptoms of low mood, anxiety, or loneliness.

Inclusion criteria for participation are (1) self-reported difficulties with low mood, anxiety, or loneliness; and (2) a score of 3 or above on the 12-item General Health Questionnaire (GHQ-12), indicating the presence of psychological distress. Exclusion criteria are the presence of severe mental health symptoms, such as self-harm or suicidal ideation, as the Tuned In program has not yet been trialed with individuals experiencing more acute mental health conditions.

Interested participants who do not meet the inclusion criteria will be provided with an information sheet about community counseling services. Eligible participants who confirm their enrollment will be randomized.

### Sample Size Calculation

Dingle and Fay [6] found a medium effect size (η^2^_p_=0.076) for improved emotion regulation after the music intervention with young adults, compared with the control group. Based on this medium effect size, at least 98 participants are needed to detect a significant group × time interaction effect (*P*<.05). However, based on previous trials, some dropout is expected after the intervention has commenced. The estimated attrition rate is 15%. Besides, considering that partnerships with middle schools have only recently begun to develop, while many university students have already expressed interest in committing to the project, we expect to recruit more university participants. Therefore, we aim to recruit over 100 participants for the randomization stage, including around 50 adolescents and 65 young adults, to account for possible dropouts before the intervention begins.

### Contingency Plan

Based on prior trials of Tuned In, we expect a high retention rate among youth [6]. However, some attrition may occur among adolescents [25]. Even with that attrition rate, we anticipate retaining at least 30 adolescents at the postintervention stage, providing sufficient data from this pilot study to inform future large-scale trials. In the event of significant challenges in recruiting adolescents, our backup plan is to recruit additional youth from the university community for this trial.

Because of the online mode of intervention, the study design minimizes potential disruptions arising from any local changes in the COVID-19 pandemic situation. If difficulties or delays in participant recruitment arise, we will place advertisements on social media as an additional recruitment channel.

Considering the risk of potential emotional disturbances, a page listing several 24-hour community crisis support hotlines has been incorporated into the manual to provide participants in need with an additional channel to external resources. Alongside the distribution of these resources, the research assistant will also give instructions on how to use them during the group contracting phase and explicitly encourage participants to seek help and notify the research assistant immediately if they experience emotional distress during the session.

In situations where psychological distress is identified either by a facilitator or self-reported by a participant, the research assistant will separate the individual from the rest of the group, while the music therapist continues to lead the remaining activities. The research assistant will provide immediate emotional support and conduct a timely risk assessment, and the principal investigator will be informed of the situation. Based on the participant’s condition, appropriate referrals will be made as necessary.

The research assistant will follow up with individuals who disclose intentions or actions related to self-harm, suicide, harm to others, or breaches of the law, and will discuss with them the appropriateness of continuing in the project or the available options for discontinuation.

### Description of the Intervention

The project consists of 5 weekly sessions: 1 introductory (preassessment) session followed by 4 psychoeducational sessions. Each session lasts approximately 60-90 minutes.

In the introduction session, participants sign the informed consent forms after being informed about the program’s content and expectations by the main group facilitator (ie, the research assistant). For participants under 18 years of age, parental consent will also be obtained during the session. Following the signing of consent, the baseline survey will be distributed and collected. Participants’ demographic information will be gathered through the survey. This includes, but is not limited to, age, gender, education level, household income, region of residence, living arrangement, and employment status.

Each week, participants will receive WhatsApp (Meta Platforms, Inc.) text message reminders about upcoming sessions and other important announcements.

The psychoeducational sessions differ in theme but follow a similar structure. Session 1 focuses on emotions located in various quadrants of the 2D model, such as high-arousal and negative-valence emotions. Session 2 explores happiness and loneliness, with the new component of loneliness added to this session. Sessions 3 and 4 address high-arousal emotions, such as stress and anxiety. An example session plan is provided in Multimedia Appendix 1 for reference (Table 1).

**Table 1 table1:** Summary of session content.

Session	Content
Session 1	Emotions located in various quadrants of the 2D model, such as high-arousal and negative-valence emotions
Session 2	Happiness and loneliness
Session 3	High-arousal and negative-valence emotions, such as stress and anxiety
Session 4	High-arousal emotions, such as perfectionism and anxiety (continue) and achievement

For the new loneliness component, in addition to discussing songs that evoke a sense of receiving empathy, psychoeducation will be provided on the positive effects of music sharing in building and strengthening emotional bonds in relationships [12]. The group sessions will offer a safe and pleasant environment where participants can talk about music, using this topic as a channel to foster new connections with fellow group members. In session 2, participants will be guided to discuss how they can apply this skill outside of the program to strengthen existing relationships and build new connections.

Participants are also expected to select music for themselves during the group sessions. These self-selected songs serve to evoke the target emotions for each session and support group discussions and experiential psychoeducation—specifically, increasing awareness of the bodily or physiological changes that accompany each emotion as elicited by music. As music appreciation is used as a tool to support psychoeducation about emotions, rather than being a goal in itself (ie, the program is not intended to enhance musical understanding), we believe that participant-selected songs are more appropriate than those prescribed or suggested by the program facilitators. This is also in line with literature supporting the benefits of using self-selected and familiar music [21]. As such, participants’ sharing of their self-selected music is incorporated as a core element in the sessions. The music submitted by participants spans a wide range of styles, reflecting their individual tastes, and includes Cantonese pop songs, classical music, movie soundtracks, and more.

Each session begins with a music check-in led by the music therapist, followed by participants listening to their self-selected music. This music listening and sharing segment takes approximately 15-20 minutes. Once the target emotions are evoked, the research assistant provides psychoeducation on the theme emotion and facilitates a group discussion on coping strategies. Around 10-15 minutes are allocated for this group discussion. Next, the music therapist guides participants through a core music activity designed to support reflection and reconnection with the theme emotion. Selected music activities include body scan, drawing, and lyric analysis. Each activity takes approximately 15 minutes. Each theme emotion is paired with its own specific psychoeducational content and corresponding music activity. The session concludes with a summary and debriefing provided to participants.

By the end of the last session, participants will be invited to complete the postquestionnaire. Individuals who complete both the prequestionnaire and postquestionnaire will receive a reimbursement of HK $200 (US $25.77) in cash. Reimbursement will be provided in person, and participants will be required to sign a receipt for record-keeping purposes. The intervention for the control group will be delivered after the final session of the experimental group and upon completion of the postquestionnaire by its participants. A flowchart outlining the project has been included in Multimedia Appendix 2.

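### Participants are randomised and told their arm before they sign consent and complete the baseline survey, so the pre score is a post-allocation measure

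*Protocol article*

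**What the plan says.** The order of events has to be assembled from three sections of the Methods in the Protocol article.

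- **Participants:** "Eligible participants who confirm their enrollment will be randomized". Signed consent is not named as a condition.
- **Randomization and Blinding:** "randomization will be conducted, typically 2 weeks before the intervention start date". The next step is disclosure: "Participants will then be informed of their group allocation, along with the schedule of their assigned group sessions, by the designated research assistant".
- **Description of the Intervention:** "The project consists of 5 weekly sessions: 1 introductory (preassessment) session followed by 4 psychoeducational sessions". Consent belongs to the first of these: "In the introduction session, participants sign the informed consent forms". Parental consent for those under 18 is taken in the same session. Then: "Following the signing of consent, the baseline survey will be distributed and collected". That survey also collects the demographics.

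Three other sections bear on the point. Ethical Considerations requires a signed form before a person takes part in the intervention, not before randomisation. Data Analysis uses the pre score as one of the two levels of time in a mixed ANOVA, and picks covariates by testing baseline demographics between groups. Sample Size Calculation sets the number to be randomised "to account for possible dropouts before the intervention begins", so some loss after randomisation is foreseen.

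**The concern.** A baseline is protected by randomisation only if it is fixed before anyone knows the arm. Here the outcomes are self-reported (Limitations), the control is a waitlist, and each participant knows whether the programme comes now or later when answering the pre survey. The group × time contrast is the difference between arms in post minus pre. Any shift in one arm's pre score caused by that knowledge therefore passes one-for-one into the primary estimate. The demographic tests that select covariates also use data collected only from people who stayed after learning their arm.

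The second risk is selection. Participants, and parents of minors, first give written consent when the arm is known, so refusal can depend on the arm. People who leave at that point are randomised but have no signed consent, no baseline outcome score and no survey demographics. They cannot enter an analysis of the outcome scales by arm as randomised.

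**Working it through.** **1. The order of events.** The five sessions are weekly and the introductory one comes first, so it falls about 1 week before the first psychoeducational session.

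| Meaning of the start date | Randomisation | Consent and baseline | Allocation known before baseline by |
|---|---|---|---|
| First psychoeducational session | about 2 weeks before | about 1 week before | about 1 week |
| Introductory session | about 2 weeks before | at the start date | about 2 weeks |

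Allocation comes first under both readings. The article does not say separately when waitlist participants attend the introductory session. If it were tied to their own later start, it could not supply a pre-waiting baseline, so that gap does not restore the usual order.

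**2. The plan's own sample size.** Inputs from Sample Size Calculation: partial eta squared 0.076, significance level 0.05, N = 98. Power is not stated; 80% and a two-sided test are assumed.

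- f = √(0.076 / 0.924) = 0.287, and d = 2f = 0.574 SD of the change score.
- Noncentral F test with 1 numerator degree of freedom and noncentrality N·f²: N = 98, power 0.803. The normal approximation gives 96.
- Inflated for the stated 15%: 98 / 0.85 = 115.3, so 116, against the planned 50 + 65 = 115.

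The figure of 98 reproduces and is not at issue.

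**3. What a shifted baseline would do (illustration).** The article gives neither a pre-post correlation ρ nor a size for any shift, so both are assumed. The SD of change is √(2(1−ρ)) raw SDs, and the planned effect in raw SDs is 0.574 × √(2(1−ρ)). The bias as a share of the planned effect is the shift divided by that value.

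| ρ | Planned effect (raw SD) | Shift 0.05 SD | Shift 0.1 SD | Shift 0.2 SD |
|---|---|---|---|---|
| 0.5 | 0.574 × 1.000 = 0.574 | 8.7% | 17.4% | 34.9% |
| 0.6 | 0.574 × 0.894 = 0.513 | 9.7% | 19.5% | 39.0% |
| 0.7 | 0.574 × 0.775 = 0.444 | 11.3% | 22.5% | 45.0% |

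**4. What loss before the survey would do (illustration).** No rate is given, so a range is assumed on top of the stated 15%, starting from 115 randomised. The number with both scores is 115 × (1 − early loss) × 0.85, rounded down.

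| Assumed early loss | With both scores | Power |
|---|---|---|
| 0% | 97 | 0.80 |
| 5% | 92 | 0.78 |
| 10% | 87 | 0.75 |
| 15% | 83 | 0.73 |
| 20% | 78 | 0.71 |

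The loss of power is secondary. What matters more is whether the early loss differs by arm, and the table cannot show that.

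**The case against.** The best defence is that the order is inferred. What confirming enrolment involves is not defined, the interval is only typical, and the flowchart (Multimedia Appendix 2), the natural place for the sequence, is not shown. This is also a seed-funded pilot in which the post score is in any case self-reported with the arm known. These points are fair, but no section places consent or the baseline survey before randomisation, and the text should not need a flowchart to reverse its order. An unblinded post score is hard to avoid with a waitlist; an unblinded pre score can be avoided.

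Several stronger readings are tempting and are not supported:

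- **That 15% of those randomised, about 17 of 115, would be lost before baseline.** Sample Size Calculation attaches the 15% to dropout once the intervention is under way. No rate is given for the earlier interval.
- **That people lost early have no data at all.** Screening responses exist, including the GHQ-12 used for eligibility.
- **That everyone who drops out before the intervention lacks a baseline.** If the intervention begins with the first psychoeducational session, a person who leaves in the week after the introductory session has both consent and baseline.
- **That rapport-building contaminates the pre score.** The introductory session is meant to build rapport, but nothing says those activities come before the survey.
- **That the bias favours the programme, or that refusal will concentrate in the waitlist arm.** The article gives no basis for either direction.

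**Conclusion.** The point holds as a problem of stated sequence. On the text as written, allocation is disclosed about 1 to 2 weeks before written consent and the self-reported baseline. The pre score in the primary contrast and the variables that select covariates are thus post-allocation measures, and refusal can depend on the arm. An analysis plan written later cannot recover a pre-allocation baseline, so this is not a detail that can be left to one.

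The size is unknown. The range of about 9 to 45% of the planned effect (17 to 22.5% for a 0.1 SD shift) rests wholly on the assumed shift and correlation. It shows only that a modest shift would not be negligible beside the planned effect. The sample size of 98 is unaffected. Because the order touches both the primary estimate and who contributes to it, it should be corrected for every batch not yet randomised.

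**What to change.** 1. Obtain signed participant consent, and parental consent for those under 18, then collect the full baseline survey. Qualtrics is already used for screening and for the outcome measures.
2. Only then have the independent researcher randomise and release the allocation.
3. Keep the introductory session for rapport-building, after the baseline has been collected.
4. Define the analysis set as all consented participants with a baseline who are then randomised.
5. State when waitlist participants give their baseline, and make the Methods text and the flowchart agree on the order.
6. For batches already randomised under the present order, report by arm the number lost between allocation and the baseline survey, and name the post-allocation baseline as a limitation.

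The cost is an ethics amendment (two universities gave approval) and collecting physical consent forms, including parental ones, about 2 weeks earlier, possibly with one more document exchange. No new measures are needed and the target of 98 does not change.
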